## Abstract

**Introduction:**

Patients with cerebral hemorrhage often require a tracheal intubation to protect the airway and maintain oxygenation. Due to the use of analgesic and sedative drugs during endotracheal intubation and the opening of the glottis may easily cause aspiration pneumonia. Ceftriaxone is a semi-synthetic third-generation cephalosporin with strong antimicrobial activity against most gram-positive and gram-negative bacteria. It can effectively prevent and treat aspiration pneumonia.

**Methods and analysis:**

This is a prospective, randomized, controlled, double-blind clinical study. Patients with intracerebral hemorrhage (ICH) undergoing endotracheal intubation in Dong E Hospital of Shandong Province from April 2023 to April 2025 will be enrolled and randomly assigned to the intervention group or control group. The intervention group will be treated using 100mL 0.9% sodium chloride with 2g ceftriaxone intravenously over the course of one hour beginning within two hours after endotracheal intubation. The control group will be given 100mL 0.9% sodium chloride injection intravenously of the course of one hour beginning within two hours after endotracheal intubation. The primary outcome is the incidence of aspiration pneumonia within 48 hours after endotracheal intubation. Secondary outcomes include: intensity of antimicrobial use, length of hospital stay, duration without mechanical ventilation, and 28-day mortality.

**Discussion:**

The primary objective of this study is to explore whether a single dose of ceftriaxone administered during endotracheal intubation in patients with ICH reduced the incidence of pneumonia within 48 hours and provide evidence for the prevention of aspiration pneumonia in patients with ICH with endotracheal intubation.

**Trial registration:**

The trial is registered at the Chinese Clinical Trial Registry: ChiCTR2200066837. Registered on December 19, 2022.

## Introduction

Patients with intracerebral hemorrhage (ICH) often experience such complications as consciousness disorders, respiratory center damage, airway obstruction, and swallowing dysfunction [1]. Endotracheal intubation is often required to protect the airway and maintain oxygenation [2]. However, during intubation, analgesic and sedative drugs are administered and the glottis is exposed, allowing oral secretions to easily to enter the lower respiratory tract and cause aspiration pneumonia [3–5]. Inhaled substances may include secretions from the nasal cavity and oropharynx, residual food in the mouth, contents of gastrointestinal vomiting, and digestive fluid reflux, which may cause aspiration pneumonia [6]. One type of aspiration pneumonia is chemical inflammation caused by direct damage to lung tissue caused by inhalation of gastric contents; another type is pulmonary atelectasis and inflammation caused by inhalation of obstructive substances; and the third type is bacterial pneumonia caused by inhalation of oral secretions containing colonized bacteria, which is the most common clinical type and can be fatal in severe cases [7]. Studies have shown that the expected mortality of patients with aspiration pneumonia is higher than that of patients with other forms of pneumonia [8].

Pneumonia caused by inhalation of anaerobic bacteria may be subacute because of the low virulence of the bacteria, but its clinical features are difficult to distinguish from other bacterial pneumonitis [9]. While both aspiration pneumonia and aspiration pneumonitis result from the inhalation of foreign substances into the lungs, they differ in terms of the infectious nature of the lung injury. Aspiration pneumonia involves a bacterial infection following an aspiration event, whereas aspiration pneumonitis is characterized by an inflammatory reaction to irritative gastric contents without the development of bacterial infection. Clinicians should be aware of the differences between these conditions to ensure appropriate management and treatment.

A prospective observational study involving a total of 879 cases of emergency endotracheal intubation patients found that, after excluding patients who were not eligible for prognostic assessment (those who died within 48 hours without detection of pneumonia), 8.0% (66/823) developed aspiration pneumonia that may have been associated with emergency intubation [10]. A large study from a single center in Japan showed that the incidence of aspiration pneumonia in elderly patients (aged >70) was 67.2 per 10,000 people from 2010 to 2015, and the mortality rate was 13.6% [11]. A retrospective study including patients with an average age of 78 in a single center in South Korea showed that the 1-year mortality rate of patients with aspiration pneumonia was 49.0% [12]. Even when the data are corrected, the case fatality rate of aspiration pneumonia is still higher than that of other forms of pneumonia [12]. Therefore, the prevention of aspiration pneumonia is particularly important.

Conventional measures to prevent aspiration pneumonia include: elevation of the head of the bed, good oral care, swallowing function assessment and training, comprehensive rehabilitation, nasogastric feeding, improvement of gastric emptying function, and monitoring of gastric residual volume [13]. Given the pathophysiology of aspiration pneumonia and infection caused by aspiration, the application of antibiotics before endotracheal intubation can be regarded as a preventive strategy. In the *Expert Advice on the Diagnosis and Treatment of Aspiration Pneumonia in Adults*, the preventive measures for aspiration pneumonia are recommended as ‘antibiotic treatment for 24 hours after emergency intubation in coma patients’ [14].

Previous studies have shown that anaerobic bacterial infections are not common in aspiration pneumonia, with pathogens like *enterobacteria*, *Haemophilus influenzae*, *Streptococcus pneumoniae*, and *Staphylococcus aureus* being more prevalent in community-acquired cases, and gram-negative bacilli, such as *Pseudomonas aeruginosa*, in hospital-acquired cases [15]. Only one case of ventilator associated pneumonia was the result of an anaerobic infection [16]. In cases of post-stroke pneumonia, gram-negative bacilli (mainly *Klebsiella pneumoniae* and *Escherichia coli*) and *Staphylococcus aureus* were frequently isolated [17]. Similarly, in patients with intracerebral hemorrhage (ICH) who underwent endotracheal intubation, nosocomial respiratory infections were found in over half of the cases, with gram-negative bacteria being the predominant pathogens [18]. Ceftriaxone, a semi-synthetic third-generation cephalosporin, is highly effective against these common pathogens, making it a suitable option for preventing and treating aspiration pneumonia in these patients [19, 20].

The aim of this study is to investigate whether a single dose of ceftriaxone during endotracheal intubation can reduce the incidence of pneumonia within 48 hours in patients with cerebral hemorrhage, and to provide a basis for the prevention of aspiration pneumonia in patients with cerebral hemorrhage.

## Methods and analysis

This study was approved by the hospital ethics committees of Dong E Hospital. All methods will be performed in accordance with the relevant guidelines and regulations. Written informed consent will be obtained from the guardians of all patients and registered in the Chinese Clinical Trial Registry (Registration number: ChiCTR2200066837). All methods were reported according to Consolidated Standards of Reporting Trials (CONSORT) [21].

### Study design

This is a prospective, randomized, controlled, double-blind clinical study, which was reviewed by the ethics committee of Dong E Hospital.

### Inclusion and exclusion criteria

Patients with ICH undergoing endotracheal intubation in Dong E Hospital of Shandong Province from April 2023 to April 2024 will be included. Inclusion criteria are: (1) age > 18 years; (2) ICH due to various causes; (3) endotracheal intubation; and (4) subjects understood and signed the informed consent. The following patients will be excluded from this study: (1) pneumonia occurred before endotracheal intubation; (2) aspiration occurred before endotracheal intubation (e.g., aspiration that is considered possible clinically, such as epilepsy; prehospital vomiting; vomit on the patient’s clothing; or vomit visible in the oropharynx at the beginning of intubation attempts); (3) received antibiotics before endotracheal intubation; (4) received other antibiotics within 48 hours after enrollment (especially before diagnosis of aspiration pneumonia); (5) patients who died within 48 hours after endotracheal intubation without aspiration pneumonia; (6) allergic history to cephalosporin antibiotics; and (7) drinking history within one week before endotracheal intubation, as the use of cephalosporin after drinking alcohol can cause a disulfiram reaction. Of note, patients with COPD will not be excluded from the study. Schedule of enrolment, interventions, and assessments are shown in **Fig 1**. A simplified schematic of the trial design is shown in **Fig 2**.

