### Intervention

Subjects will be randomly assigned 1:1 to the ceftriaxone intervention group or the control group after signing informed consent on a computer-generated randomization table generated by an investigator not involved in the clinical trial. Patients who meet the inclusion criteria will undergo endotracheal intubation routinely according to the operating specifications of our unit. Patients in the intervention group will be given 100mL 0.9% sodium chloride with 2g ceftriaxone sodium intravenously over the course of one hour within two hours after endotracheal intubation. Patients in the control group will receive 100 mL 0.9% sodium chloride injection intravenously over the course of one hour within two hours after endotracheal intubation. Other treatment measures after endotracheal intubation (ie: prevention of aspiration, withdrawal of mechanical ventilation) are the same as conventional treatment. Neither the investigators nor the patients will be aware of the group assignments during the study. Open label is allowed in case of serious adverse effects such as allergic reaction.

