### Research outcomes

The primary outcome is the incidence of aspiration pneumonia within 48 hours after endotracheal intubation. Aspiration pneumonia is defined the presence of new or advanced infiltrating shadows, consolidation shadow, or ground glass shadow on chest X-ray or CT in patients without a diagnosis of community-acquired pneumonia, healthcare-associated pneumonia, or aspiration pneumonia, combined with two or more of the following clinical symptoms: (1) fever, body temperature >38°C; (2) purulent airway discharge; (3) white blood cell count >10 ×10 ^ 9 / L or<4×10^9/L. Secondary outcomes include: intensity of antimicrobial use, length of hospital stay, duration without mechanical ventilation, and 28-day mortality. A subgroup analysis will be conducted in patients with high and low aspiration pneumonia risk, which will be defined as follows: low-risk patients will exhibit none of the following intubation characteristics: visible stomach contents during intubation, aspiration suspected, and evidence of aspiration by bronchoscopy. High risk patients will exhibit one or more of the following intubation characteristics: visible stomach contents during intubation, aspiration suspected, and evidence of aspiration by bronchoscopy.

The intensity of antimicrobial use is defined as:

$\frac{\mathrm{Antimicrobial}\;\mathrm{consumption}\;(\mathrm{cumulative}\;\mathrm{DDD})}{\mathrm{Days}\;\mathrm{of}\;\mathrm{patients}\;\mathrm{admitted}\;\mathrm{in}\;\mathrm{the}\;\mathrm{same}\;\mathrm{period}}\times 100$
where DDD is the defined daily dose.

The intensity of antibiotic use in a particular patient is defined as:

$\frac{\mathrm{Antimicrobial}\;\mathrm{consumption}\;(\mathrm{cumulative}\;\mathrm{DDD})}{\mathrm{Days}\;\mathrm{of}\;\mathrm{hospital}\;\mathrm{stay}}\times 100$

$\frac{\mathrm{Antimicrobial}\;\mathrm{drug}\;\mathrm{consumption}/DDD}{\mathrm{Days}\;\mathrm{of}\;\mathrm{hospital}\;\mathrm{stay}}\times 100$

$\frac{\mathrm{Single}\;\mathrm{dose}\;\mathrm{of}\;\mathrm{antibiotics}\times \mathrm{frequency}\;\mathrm{of}\;\mathrm{use}\times \mathrm{days}\;\mathrm{of}\;\mathrm{use}/\mathrm{DDD}}{\mathrm{Days}\;\mathrm{of}\;\mathrm{hospital}\;\mathrm{stay}}\times 100$

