### Statistical analysis

SPSS 20.0 will be used for statistical analysis. Demographic factors and baseline characteristics, such as age, sex, APACHE II score, and SOFA score, will be adjusted for using appropriate statistical methods. These adjustments may include logistic regression for binary outcomes or stratified analysis if needed. The primary outcome, which is the incidence of aspiration pneumonia within 48 hours of intubation, will be compared between the control and intervention groups using either the chi-square test or Fisher’s exact test, depending on the distribution of the categorical data. For the secondary outcomes, continuous variables like length of ICU stay, duration of mechanical ventilation, and hospital length of stay will be described using mean ± standard deviation or median (interquartile range) depending on the distribution of the data. Differences between the groups will be tested using independent t-tests for normally distributed data or Mann-Whitney U tests for non-normally distributed data. Categorical outcomes such as 28-day mortality will be analyzed using chi-square or Fisher’s exact test. For any time-to-event outcomes, such as the time until the development of aspiration pneumonia or extubation, Kaplan-Meier survival analysis will be used, with differences between the groups assessed via the log-rank test.

In terms of assumptions, the study will check for normality and independence in the data, particularly for tests like the t-test or chi-square test. If assumptions of normality are violated, appropriate data transformations (e.g., logarithmic transformation) or non-parametric tests will be used. For categorical data, Fisher’s exact test will be used if expected cell counts are less than 5 in any of the categories. Missing data will be handled using a complete case analysis, where possible. If missing data is substantial, multiple imputation techniques will be applied to ensure the integrity and reliability of the analysis.

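### Exclusion criteria (4) and (5) are post-randomisation events in the primary-outcome window, so applying them removes randomised patients for reasons tied to the outcome

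*Protocol article*

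**What the plan says.** The Inclusion and exclusion criteria section lists the patients who are to be excluded from the study. Two items on the list refer to the future course of the patient. One is "4) received other antibiotics within 48 hours after enrollment (especially before diagnosis of aspiration pneumonia"; the other is "5) patients who died within 48 hours after endotracheal intubation without aspiration pneumonia".

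The Intervention section states: "Subjects will be randomly assigned 1:1 to the ceftriaxone intervention group or the control group after signing informed consent". The study infusion is given "intravenously over the course of one hour within two hours after endotracheal intubation".

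Under Research outcomes, "The primary outcome is the incidence of aspiration pneumonia within 48 hours after endotracheal intubation". The secondary outcomes are "intensity of antimicrobial use, length of hospital stay, duration without mechanical ventilation, and 28-day mortality".

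Statistical analysis says: "Categorical outcomes such as 28-day mortality will be analyzed using chi-square or Fisher’s exact test". It names no analysis population for mortality or for any other outcome. For missing data it offers complete-case analysis, or multiple imputation if the missing data are substantial.

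**The concern.** An exclusion criterion should be assessable before assignment. These two cannot be: each describes something that happens over the following 48 hours, when the patient has already been randomised and usually dosed. Following the rule means dropping randomised patients.

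The two criteria do this in different ways.

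- **Criterion (4) lies on the path to the outcome.** Fever, purulent secretions and an abnormal white cell count are components of the pneumonia definition, and they are also signs that can prompt antibiotics. The criterion singles out treatment before diagnosis, so it removes evolving pneumonias treated on suspicion. Read literally, it also removes diagnosed cases treated within the 48 hours, which are the primary events themselves. It truncates antimicrobial intensity too, because patients with early antibiotic use leave the analysis.
- **Criterion (5) is a competing event.** A patient who dies by 48 hours is kept only if pneumonia came first. Removal is conditional on the primary outcome, so the removed share differs between arms whenever ceftriaxone prevents pneumonia, even if it has no effect on death.

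At stake is the randomised comparison for pneumonia, antimicrobial intensity and 28-day mortality. The Discussion presents randomisation as this trial's advantage over an earlier non-randomised study with biased control selection. These criteria give part of that advantage away.

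**Working it through.** **1. Timing.** The study infusion must be assigned before it is given, and it is given within two hours after intubation. Randomisation is therefore complete by about hour 2 at the latest. For criterion (5) at least 48 − 2 = 46 of the 48 hours lie after the infusion is due to start. Criterion (4) counts forward from enrolment. The primary outcome uses the same 48 hours.

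**2. Does anything restore these patients?** Statistical analysis names no all-randomised population. Its missing-data rules deal with missing values and do not bring back patients whom the exclusion list has removed.

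**3. Inputs.** From Sample size calculation: pneumonia 16% (ceftriaxone) and 32% (control), two-sided 5% level, 177 per arm inflated for 10% loss to 177/0.9 = 197. The inflation reproduces. The 177 does not follow from the stated rates at 80% power (pooled formula: 111). That is a separate matter and is not used here; the calculations take 197 randomised per arm as planned. All other rates are assumptions.

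**4. Criterion (4).** Assume a share f of would-be pneumonias receives other antibiotics and is excluded. With true rate p,

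- analysed rate = p(1 − f)/(1 − pf)
- analysed number per arm = 197(1 − pf)

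| f | Control | Ceftriaxone | Difference (points) | n control / ceftriaxone | Power |
|---|---|---|---|---|---|
| 0 | 32.0% | 16.0% | 16.0 | 197 / 197 | 97% |
| 25% | 0.24/0.92 = 26.1% | 0.12/0.96 = 12.5% | 13.6 | 181 / 189 | 92% |
| 50% | 0.16/0.84 = 19.0% | 0.08/0.92 = 8.7% | 10.4 | 165 / 181 | 81% |
| 75% | 0.08/0.76 = 10.5% | 0.04/0.88 = 4.5% | 6.0 | 150 / 173 | 55% |

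Power is by exact enumeration of the uncorrected chi-square test; a normal approximation gives 96.3%, 91.5%, 80.0% and 53.8%. At f = 100%, the literal reading if every case is treated within 48 hours, no primary events remain.

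**5. Criterion (5), no drug effect on death.** Assume death by 48 hours at rate e in both arms, independent of pneumonia, and true 28-day mortality of 30% in both arms. For e, the Introduction cites a general emergency-intubation cohort in which 879 − 823 = 56 patients were set aside as early deaths without pneumonia, so e = 56/879 = 6.4%.

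- Removed share = e(1 − p). Ceftriaxone: 0.0637 × 0.84 = 5.4%. Control: 0.0637 × 0.68 = 4.3%.
- Analysed mortality = (0.30 − removed)/(1 − removed). Ceftriaxone: (0.30 − 0.0535)/(1 − 0.0535) = 26.0%. Control: (0.30 − 0.0433)/(1 − 0.0433) = 26.8%.

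The false benefit for ceftriaxone is 0.8 points. It is 0.35 points at e = 3%, 1.3 at 10% and 3.1 at 20%.

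**6. Criterion (5), drug effect on early death.** Assume early death without pneumonia is 10% vs 5% (ceftriaxone vs control), and all other 28-day deaths are 25% in each arm. True mortality is 35% vs 30%. After exclusion it is 0.25/0.90 = 27.8% vs 0.25/0.95 = 26.3%. A 5-point harm is reported as 1.5 points.

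**The case against.** The best defence has four parts.

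- **An analysis plan or full protocol may define an all-randomised set.** It may, but it would have to contradict an explicit exclusion rule in this article. The finding rests on what is stated.
- **The trial is double-blind.** This stands in part: blinding limits differential prescribing. A reader might push the antibiotic criterion to a large false-positive risk. With equal true rates of 24% and removal of 0% of cases in one arm and 25% in the other, the analysed rates are 24.0% vs 19.1% and the test rejects about 21% of the time. Nothing in the document supports so lopsided a split under blinding. Blinding does not, however, stop the drug from changing the signs that prompt antibiotics, or whether pneumonia precedes death.
- **The cited cohort also removed early deaths.** That was an observational incidence estimate with no randomised comparison to protect.
- **The 10% loss allowance covers it.** The allowance adds patients; it does not remove bias.

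Three stronger readings are not supported.

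- A reader might add criterion (2), since vomit seen at the start of intubation could be found after randomisation. The text leaves the order of consent, randomisation and intubation open; intubation is itself an inclusion criterion, so randomising afterwards fits. A finding made before the study drug is also not affected by it.
- A reader might argue that the removals leave fewer than 177 per arm and an underpowered trial. Even 148 per arm gives about 90% power at 16% vs 32%, so falling below 177 shows no inadequacy.
- A reader might say that all early deaths vanish. Only those without aspiration pneumonia do.

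**Conclusion.** The point holds for criteria (4) and (5) and should be corrected before the analysis. The stated rule produces a non-randomised comparison for the primary outcome and for 28-day mortality, and a truncated one for antimicrobial intensity. This follows from the timing alone and needs no assumed rate.

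The size is uncertain. The document gives no early-death, 28-day mortality or early-antibiotic rates for this population, and the 6.4% comes from a different one. Under the assumptions shown, criterion (4) shrinks a 16-point difference to 13.6 or 10.4 points when 25% or 50% of cases are lost. Criterion (5) creates a false mortality benefit of about 0.8 points at 6.4% early death (0.35 to 3.1 points over 3% to 20%). That is small if the drug does not affect early death, but a true early harm could be largely hidden. A fall in overall reported mortality, the same in both arms, would be a change of level and not evidence of bias between arms.

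**What to change.** 1. Delete (4) and (5) from the exclusion list and keep only criteria that can be assessed before randomisation.
2. Follow every randomised patient and analyse each in the assigned group, for all outcomes including 28-day mortality.
3. Record other antibiotics given within 48 hours and do not exclude for them. Add a sensitivity analysis that counts antibiotics started for suspected pneumonia as events.
4. Prespecify how death within 48 hours without pneumonia is handled. Report pneumonia alone and pneumonia-or-death by 48 hours, naming one as primary and the other as sensitivity. Either choice is defensible. Counting such deaths as non-events can favour an arm with more early deaths, so the pair should be shown together.

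**Cost.** Protocol wording, a few added analyses and no increase in the number randomised. Antibiotic use after enrolment and 28-day survival are already on the data collection list, but patients who would have been dropped now need complete 48-hour assessment and 28-day follow-up. Early use of other antibiotics will dilute the contrast slightly in the all-randomised analysis.
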